### Concealment mechanism {16b}

Due to the utilization of a cluster randomization method, we do not conceal the allocation. As a result, the proposed concealment mechanism is not applicable in this scenario. The allocation sequence will be securely concealed and not disclosed until all centers are recruited and baseline data are collected.

### Implementation {16c}

An investigator will use a randomization algorithm to allocate six candidate sites to different groups, ensuring random and unbiased assignment. The results will be informed to the social workers at respective sites. At each site, social workers will be responsible for recruitment and conducting baseline assessments. All subjects who have provided informed consent will be included in the trial. The social workers will guide the enrollment session, explaining the intervention assignment process to the participants. Following enrollment, the overarching purpose of the study, intervention procedures in the assigned group, and measurement details will be thoroughly explained to each participant. Additionally, each participant will undergo a baseline assessment that includes collecting information on socio-demographics, dietary behaviors, anthropometric characteristics, medical history, and nutritional status.

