### Trial design {8}

This experimental study expected to run from July 2023 to September 2024 will follow a non-blinded, paralleled, two-arm pre-test post-test design including 150 community-dwelling elders. This trial will be conducted simultaneously in six community health service centers within Nanhu district, Jiaxing City, located in Zhejiang province, China. Following a cluster randomization design, intervention and control sites will be allocated in a 1:1 ratio based on a randomized allocation sequence generated by a single investigator using R 4.2.0 The intervention period is expected to last for 6 months, following a preparation and recruitment phase. Effect measurements will be conducted at three time points: at the beginning, after 3 months, and after 6 months of the intervention. Implementation measurements will be carried out throughout the study. The trial design follows the SPIRIT checklist (Additional file 1).

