### Who will take informed consent? {26a}

Eligible elderly individuals will be invited to attend the enrollment session, where trained social workers will explain the study in detail. Considering the potential literacy and functional limitations in this demographic, these social workers will use simplified language and visual aids to facilitate comprehension. Participants will receive a consent package containing clear information about the study’s purpose, procedures, risks, and benefits, as well as the assurance of the confidentiality of their data, which will be accessible only to investigators. They will have ample time for review and understanding. Social workers will answer questions and address concerns, ensuring full understanding before participants sign the informed consent forms. This process will occur before any allocation or baseline assessment.

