### Recruitment {15}

A convenience sampling method will be used to recruit community-dwelling elders from six communities mentioned in section {8}. Patients will be primarily recruited through three methods: (1) posting flyers at primary care centers during regular physical examinations of community-dwelling elderly individuals, (2) recommendations from community healthcare professionals during clinical appointments at community health service centers, (3) recommendations during community healthcare professionals’ regular home visits with elderly individuals. Additionally, the staff of the community health service center sent recruitment messages. We expect the physical examination to serve as the primary recruitment channel. Trained social workers will assist potentially eligible patients in confirming their eligibility. Eligible elderly individuals will receive invitations to attend the enrollment session, during which the social workers will provide instructions on participation procedures, and interested individuals will be given a consent package.

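### The protocol contradicts itself on when site allocation is disclosed; if disclosure comes before recruitment, recruiters who know the arm can influence who enters the trial

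*Protocol article*

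**What the plan says.** The trial randomises sites, not people: "intervention and control sites will be allocated in a 1:1 ratio based on a randomized allocation sequence" (Trial design {8}), and "An investigator will use a randomization algorithm to allocate six candidate sites to different groups" (Implementation {16c}). Individuals are then enrolled within sites: "A convenience sampling method will be used to recruit community-dwelling elders" (Recruitment {15}).

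On concealment, {16b} makes two statements in one short paragraph. It begins "Due to the utilization of a cluster randomization method, we do not conceal the allocation" and adds that a concealment mechanism does not apply. It ends "The allocation sequence will be securely concealed and not disclosed until all centers are recruited and baseline data are collected".

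The consent section {26a}, after describing how social workers explain the study and obtain signatures, says "This process will occur before any allocation or baseline assessment".

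Implementation {16c} has the sites allocated and continues "The results will be informed to the social workers at respective sites. At each site, social workers will be responsible for recruitment", with baseline assessments added to the same workers' duties. It goes on to say that the procedures of the assigned group are explained after enrolment, and then describes the baseline assessment.

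**The concern.** In a cluster trial that recruits individuals, a single disclosure reveals the arm of every later recruit at that site. Concealment from the people who recruit is therefore at least as important as in an individually randomised trial, and the use of cluster randomisation is no reason to drop it.

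Here the social workers are the recruiters. They help confirm eligibility ({15}), explain the study and handle consent ({26a}), and recruit and assess at baseline ({16c}). With convenience sampling there is no fixed list against which omitted elders could be seen. A worker who knows that the site offers a canteen-based recommendation service could favour elders likely to use it. That disposition is closely related to dietary diversity, diet quality and adherence, and the covariates listed under Statistical methods {20a} do not measure it directly. Differences in who enrols would then be mixed with the intervention effect, and a larger sample would not remove them.

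**Working it through.** The protocol gives no figure for this point, so the check sets the statements side by side.

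1. **{16b}, opening.** Allocation is not concealed: "we do not conceal the allocation". No timing is given.
2. **{16b}, closing sentence.** Allocation is withheld until centres are recruited and baseline data are collected. This is explicit timing, and it is protective.
3. **{26a}.** Consent precedes both allocation and baseline assessment. This is also explicit and protective.
4. **{16c}.** In written order: sites allocated; social workers told; social workers responsible for recruitment and baseline assessment; enrolment session; assigned-group procedures explained; baseline assessment described. No time marker ties disclosure to recruitment, so the order comes only from the sequence of sentences.

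Statements 1 and 2 cannot both be true. Statements 2 and 3 agree with each other. Statement 4, carried out as written, conflicts with both.

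**Do other safeguards close the gap?** Sequence generation {16a} keeps the person who generates the sequence away from centre recruitment and participant data. Who will be blinded {17a} blinds the data analysts only. Neither covers the social workers.

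**Which step is exposed?** {16c} includes everyone who consents, so there is no selection after consent. The exposed steps are approaching elders and checking eligibility.

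**Which T0 measurements are exposed?** Table 2 under {18a} gives the IoT system log as the source for dietary diversity, diet quality and adherence. Outcomes {12} makes these the primary outcomes. MNA-SF and anthropometry are collected by questionnaire and body measurement, and {12} classes them as exploratory. An assessor who knows the arm mainly threatens the second group.

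**Can the bias be sized?** Only by assuming a selection difference. Suppose, purely as an assumption, that selection shifts DDS by 0.2 SD, with σ = 6.12 and δ = 2.3 from Sample size {14}:

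- Shift: 0.2 × 6.12 = 1.22 points.
- Carried over in full (arm comparison ignoring baseline): 1.22 / 2.3 = 53% of δ.
- Adjusted for baseline with ρ = 0.7: (1 − 0.7) × 1.22 = 0.37 points, and 0.37 / 2.3 = 16% of δ.
- Change from baseline with a constant shift: 1.22 − 1.22 = 0, or 0% of δ.

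One assumed input thus gives anything from 0% to 53%. Selection on responsiveness to the intervention would not cancel at baseline, and this range does not cover it.

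**The case against.** The strongest reply is that {16c} never says when the workers are told, whereas the two sentences that do state timing ({26a} and the end of {16b}) both describe the safe order. On that view {16c} is a loose summary and the trial may well have been run with allocation concealed. The point about timing stands: recruitment by informed workers is a risk under one reading and not something the protocol establishes. It does not remove the contradiction, because {16b} also says outright that allocation is not concealed, and a site working from {16c} in its written order would recruit with the arm known.

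Three stronger inferences are tempting but not supported:

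- **Elders choose to join knowing their arm.** {16c} places the explanation of assigned-group procedures after enrolment and says that the assignment process is explained at the enrolment session. {26a} puts consent before allocation. Nothing says that elders know their arm when they consent.
- **Unblinded workers distort the primary outcomes at T0.** {16c} does list dietary behaviours in the baseline assessment, but the stated collection method is the system log and not a worker's judgement.
- **The bias is about half the target effect.** The 53% needs an assumed 0.2 SD shift carried over in full, while {12} defines the primary outcome as change from baseline.

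**Conclusion.** The contradiction is certain: {16b} conflicts with itself, and {16c} in its written order conflicts with {26a} and with the last sentence of {16b}. The bias is conditional. If site staff learned the allocation before recruitment was complete, selective approach or screening was possible and randomisation does not protect against it. If they learned it afterwards, that route is closed. The protocol does not settle which happened, and the size of any bias cannot be estimated from it.

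This must be resolved, because readers cannot otherwise tell whether randomisation protected the comparison. A reader might infer that the trial is known to have recruited with the arm known, but the text does not support going that far.

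**What to change.** Make {16b} and {16c} follow the order already stated in {26a} and in the last sentence of {16b}:

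- Eligibility checks, consent and T0 assessment are complete at all six sites before the allocation is released to any site staff.
- Arm-specific procedures are explained only after T0.
- The statements that allocation is not concealed and that a concealment mechanism is not applicable are removed.

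Trial status gives August 21, 2023 as the first enrolment, with recruitment expected to end by October 19, 2023, so some sites may already have been told. In that case, rewording alone would make the protocol inaccurate. Instead:

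- State when, and to whom, the allocation was disclosed.
- Report numbers approached, eligible and consenting by arm.
- Flag participants recruited after disclosure, and run a sensitivity analysis on them.

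The change needs no additional participants. Its cost is that sites finishing early must wait for the others. If disclosure has already happened, there is also the work of reconstructing recruitment counts and running one extra analysis.

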## Assignment of interventions: blinding

### Who will be blinded {17a}

Due to the characteristics and design of interventional studies, participants and researchers were not blinded to interventions; data analysts, however, will be blinded to the assignment of interventions.

### Procedure for unblinding if needed {17b}

Blinding is not applicable to this trial.

## Data collection and management

### Plans for assessment and collection of outcomes {18a}

All primary and secondary outcomes will be repeatedly measured at baseline, 3 months, and 6 months. System usability and satisfaction will only be evaluated in the intervention group, while dietary behaviors (dietary diversity and diet quality, adherence to the interventions), nutritional status, and anthropometric measurements will be evaluated in both the intervention and control groups. Detailed information on data collection methods is shown in Table 2.

**Table 2 Tab2:** The outcome measures and collecting methods

**Outcome measure**		**Collection method**
Dietary behavior	Dietary diversity	IoT system log, DDS
	Diet quality	IoT system log, CDGI-E
	Recommendation adherence	IoT system log
System usability and satisfaction	Satisfaction ratings	Questionnaire (CSAT)
	Ease of use ratings	Questionnaire (CES)
Nutritional status	Risk of malnutrition	Questionnaire (MNA-SF)
Anthropometric measurements	Body mass index	Basic body measurement (body weight scale, height rod)
	Waist circumference	Basic body measurement (measuring tape)
	Systolic blood pressure	Blood pressure monitor
	Diastolic blood pressure	Blood pressure monitor
	Skin folds	Basic body measurement (skinfold caliper)

### Dietary behavior

The assessment of dietary behavior encompasses three main aspects: dietary diversity, diet quality, and adherence to recommended meals. These three components are calculated based on the actual eating behaviors of elderly individuals. To track the food selections of community-dwelling elders, an IoT-based system is deployed in this trial. This system allows for the simultaneous tracking of the dishes chosen by elderly individuals for each meal, along with the check-out process. Dietary diversity will be evaluated using the dietary diversity score (DDS) [30], which has been successfully utilized to assess dietary diversity among the Chinese elderly population [31]. The diet quality of enrolled community-dwelling elders will be evaluated using China Elderly Dietary Guidelines Index (CDGI-E) [32], which is developed based on the elderly-related diet recommendations of the 2016 Chinese Dietary Guideline [33]. CDGI-E has been employed as a dietary quality evaluation index in a large-scale cross-sectional survey conducted nationwide to assess the dietary quality of the elderly [32]. Recording the actual eating behaviors allows investigators to determine the number and quantity of specific food categories in selected dishes. This information facilitates the calculation of the DDS and CDGI-E scores. Adherence to recommended meals is assessed by comparing the dishes selected by elderly individuals with the recommended ones, and the degree of adherence is recorded as the average number of matching choices to the total choices pre week.

### System usability and satisfaction

System usability and satisfaction are assessed using the ratings of satisfaction and ease of use from the intervention group. Modified Customer Satisfaction Score (CSAT) [34] on a 1 to 5 Likert scale (very unsatisfied, unsatisfied, neutral, satisfied, very satisfied) will be adopted to measure the degree of satisfaction among elderly individuals when using the recommendation system. At the end of each month, a question will be asked “How would you rate your overall satisfaction with the meal recommendation service you received?” to capture their overall satisfaction with the meal recommendation service. The perceived ease of use for the recommendation system among elderly individuals will be measured using a modified Customer Effort Score (CES) [35] on a 1 to 5 Likert scale (very difficult, difficult, neutral, easy, very easy). A question asking “On a scale of “very easy” to “very difficult,” how easy was it to understand the recommendations” will be posed at the end of each month.

### Nutritional status and anthropometric measurements

The nutritional status of community-dwelling elders will be assessed using the Mini Nutritional Assessment – Short Form (MNA-SF) [36], which offers a straightforward and efficient method for screening elderly individuals who may be malnourished or at risk of malnutrition. Anthropometric measurements will be obtained through basic body measurements and clinical blood pressure assessments. Table 2 provides a comprehensive list of the specific measuring equipment and devices used in this study.

### Plans to promote participant retention and complete follow-up {18b}

We will employ several retention strategies to minimize attrition. They include (1) confirming contact information at each assessment and obtaining contact information of two or more people who will know how to contact them; (2) providing a token of appreciation for each assessment, in addition to a small bonus gift for completing all assessments;(3) maintaining a carefully detailed tracking system with the information from both surveys and primary care center records to schedule follow-up assessments and to keep track of other retention efforts such as giving out small gifts; (4) providing daily necessities and health education materials helpful to healthy aging valued at around ¥100 (US $15) will be offered as compensation per assessment to encourage engagement and adherence of participants. In addition, we have conservatively estimated a 20% retention rate at the follow-up assessment for each study arm based on the high reported attrition rates in previous digital health interventions.

### Data management {19}

In this trial, assessment data will be collected through two methods: (1) an IoT-based ambient dietary behavior tracking system and (2) face-to-face evaluations. The assessment data will be electronically saved in an encrypted database and deidentified, with access granted only to researchers designated to control data quality and perform data analysis. Other investigators will only have read permission for the database. Double data entry and logic checks will be conducted to identify any suspicious submissions. Any suspected data errors or items with abnormal values will be logged and excluded from the final analysis. If necessary, investigators will make attempts to re-collect missing static data, such as sociodemographic and medical history. The entire process of data entry, recoding, auditing, and storage will be logged in documents, which are available from the corresponding author upon reasonable request.

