### Methods in analysis to handle protocol non-adherence and any statistical methods to handle missing data {20c}

Both intention-to-treat analysis (ITT) and per-protocol (PP) analysis will be conducted. Specifically, the interpretation of the intervention effect would be more likely to consider ITT as the gold standard approach. However, both ITT and PP analyses will be reported alongside each other for comparison. To conduct ITT analysis with incomplete data, missing data will be imputed using multiple imputation techniques.

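### The data-management rule excludes values that are only suspected or abnormal, with no confirmation of error, so genuine extreme outcomes can be deleted after allocation

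*Protocol article*

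**What the plan says.** Section {19} (Data management) describes the checks: "Double data entry and logic checks will be conducted to identify any suspicious submissions". The next sentence gives the consequence: "Any suspected data errors or items with abnormal values will be logged and excluded from the final analysis". The only recovery route named there is that, if necessary, "investigators will make attempts to re-collect missing static data, such as sociodemographic and medical history". No such route is given for flagged outcome values.

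Section {20c} plans ITT and per-protocol analyses and ranks them: "the interpretation of the intervention effect would be more likely to consider ITT as the gold standard approach". On gaps in the data it says: "To conduct ITT analysis with incomplete data, missing data will be imputed using multiple imputation techniques".

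Section {17a} says: "participants and researchers were not blinded to interventions; data analysts, however, will be blinded to the assignment of interventions". Section {19} limits working access to researchers responsible for data quality and for analysis, and gives other investigators read access only. Sections {21a} and {23} provide for an audit by the data monitoring committee (DMC) every 3 months.

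**The concern.** The rule has two triggers joined by *or*: a suspected error, or an abnormal value. Neither requires anyone to establish that the value is wrong. In this trial, abnormal values are expected. Section {10} deliberately admits people with diabetes, hypertension and hyperlipidemia, and Table 2 lists blood pressure, BMI, waist circumference and malnutrition risk among the outcomes. A high blood pressure or an unusually poor or good diet score may be exactly what was observed.

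Deleting genuine values because they are extreme makes the missingness depend on the outcome itself. If the intervention shifts the distribution, more high values are cut from one arm and more low values from the other. The difference in means then shrinks, and the remaining values look less variable than the population is. Because the decision is made after allocation and without a stated limit, it also leaves discretion over which outcomes enter the analysis.

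**Working it through.** **Step 1: the text side by side.**

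- *Trigger.* Section {19}: suspected or abnormal. Double entry and logic checks raise a suspicion. They do not by themselves show that an observed value is false.
- *Confirmation.* None is required for outcome values, although the IoT system log (Table 2 and the dietary behavior section) and the measurement records are sources to check against.
- *Consequence.* Exclusion from the final analysis, stated as something that will happen.
- *Analysis that receives the data.* Section {20c} gives ITT the leading role and imputes missing data. It does not say how values removed under section {19} are treated. If they are left out, observed outcomes are lost. If they are imputed under a missing-at-random model, that assumption fails for them, because they are missing on account of their own value.
- *Statistical need.* None from distributional shape: section {20a} chooses mixed models partly because they can handle non-normal responses.
- *Blinding.* Section {17a} blinds analysts. The status of the data-quality staff is not stated.

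**Step 2: how large the effect could be.** The plan gives no cut-off and no expected number of exclusions, so there is no figure of its own to reproduce. What follows is an illustration only.

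Inputs from section {14}: difference δ = 2.3 and SD σ = 6.12 for the dietary diversity score. Assumed here: normal scores, and deletion of values further than c SD from the pooled mean, with c = 3, 2.5 or 2.

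In SD units the arm means lie at ±h around the pooled mean, with h = δ/(2σ) = 2.3/(2 × 6.12) = 0.1879. After trimming, the mean in the upper arm is

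m = h + [φ(c+h) − φ(c−h)] / [Φ(c−h) − Φ(−c−h)],

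the retained share of the difference is m/h, and the remaining difference is 2mσ.

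- c = 3: m = 0.1879 + (0.00248 − 0.00765)/0.99682 = 0.1827
- c = 2.5: m = 0.1879 + (0.01077 − 0.02755)/0.98602 = 0.1709
- c = 2: m = 0.1879 + (0.03643 − 0.07724)/0.95068 = 0.1450

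| Cut-off | Values removed | Remaining difference | Shrinkage | Within-arm SD left |
|---|---|---|---|---|
| none | 0% | 2.30 | 0% | 6.12 |
| 3 SD | 0.3% | 2.24 | 3% | 6.03 |
| 2.5 SD | 1.4% | 2.09 | 9% | 5.82 |
| 2 SD | 4.9% | 1.77 | 23% | 5.36 |

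If the cut-off uses the SD of both arms combined, √(6.12² + 1.15²) = 6.23, the remaining differences are 2.24, 2.11 and 1.80, a shrinkage of 2%, 8% and 22%.

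Because the SD falls too, the standardised effect drops less than the raw one. At 2 SD it goes from 2.3/6.12 = 0.376 to 1.77/5.36 = 0.33, a fall of about 12%.

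If abnormal means outside a range centred on the control arm, at 2 SD, about 4.6% of control values and 6.1% of intervention values are removed, and the difference falls to 1.76. Under that rule the deletion rate itself differs by arm.

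**The case against.** The strongest case on the other side is context. The sentence follows directly on double data entry and logic checks, so it may be meant only for items that fail those checks. Nothing in the section mentions trimming at a number of SDs or removing clinically high readings. This is a fair account of the likely intent, and it is why the percentages above are hypothetical. It does not change what the sentence permits, since *abnormal* stands as a separate trigger beside *suspected error*.

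The scale could also be small. At 3 SD, 0.3% of 150 × 3 = 450 planned assessments is about one value. Exclusion might also fall on single dish or meal records rather than on the summary score, which the illustration does not model.

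There are real safeguards: exclusions are logged, data are deidentified, working access is restricted, analysts are blinded, and the DMC audits data quality every 3 months. These give oversight and an audit trail. They do not put deleted genuine values back, and blinded deletion of true extremes still attenuates the difference. It is also reasonable that re-collection covers only static data, since a past meal or a 3-month blood pressure cannot be measured again. Checking the recorded value against its source, however, remains possible.

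Query workflow and range limits commonly sit in a data management plan or SAP, and their absence here is not the point. The point is that the protocol states a definite rule, and a later document that followed it would inherit the fault.

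Three stronger readings are not supported:

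- A reader might infer that the rule contradicts ITT outright. It removes items, not participants, so everyone can stay in the allocated arm.
- A reader might infer that deleted values are imputed toward the centre. Section {20c} gives no imputation model and does not say that such values are imputed.
- A reader might infer that unblinded staff will choose the data. The blinding of data-quality staff is unstated, which does not show that it is absent.

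**Conclusion.** The point holds as a badly fixed rule. Section {19}, followed as written, excludes values on suspicion or abnormality without a confirmed error, and so allows genuine outcome values to be deleted after allocation according to their size. The expected direction is a smaller arm difference and understated variability. This sits poorly with an ITT analysis that should use every observed outcome, without being a direct contradiction of it.

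The size cannot be determined from the document. Under assumed normal scores, the planned difference and SD, and symmetric trimming of summary scores, the raw difference would shrink by about 3% at 3 SD, 9% at 2.5 SD and 22–23% at 2 SD. If the rule is in practice confined to failed logic checks, the effect could be 3% or less. A reader should not take the 2 SD figure as the expected bias. The sentence should be corrected, but it does not invalidate the design.

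**What to change.** Replace the exclusion sentence in section {19} with wording such as:

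> Flagged values will be checked against source (IoT log or measurement form) without reference to allocation. Confirmed errors will be corrected where possible. Only confirmed errors that cannot be corrected, and physically impossible values under limits fixed before data lock, will be set to missing. All other values stay in the ITT analysis.

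Add that the number of values removed will be reported by arm, and that excluding flagged but unconfirmed values will be done only as a sensitivity analysis.

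The cost is a change of wording and modest query work for the data-quality staff. The benefit is that genuine extreme outcomes remain in the main estimate and discretion over deletion is removed.
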